# STUDY POPULATION

Male/female subjects with locally advanced stage III/IV oral cancer scheduled for resection of the primary tumor and cervical lymph nodes, followed by postoperative radiotherapy or chemoradiation with curative intent, will be enrolled.

## Inclusion criteria

In order to be eligible to participate in this study, a subject must meet all of the following criteria:

1. Have a histologically confirmed diagnosis of locally advanced oral cancer (stage III/IV) which is planned for treatment with curative intent including surgical resection.
2. Be willing and able to provide written informed consent/assent for the trial.
3. Be ≥ 18 years of age on day of signing informed consent.
4. Must agree to provide tissue from fresh tumor biopsy pretreatment and from the surgical resection material to determine the actual PD-L1 status and perform immunomonitoring/DNA/RNA profiling.
5. Willing to allow up to two additional biopsies when baseline [^18^F]BMS-986192 PET /[^18^F]-FDG PET scans show heterogeneous and/or discrepant uptake.
6. Have a performance status of 0-1 on the ECOG Performance Scale ([Appendix 2](#_APPENDIX_2:_Eastern)).
7. Demonstrate adequate organ function as defined in table 1. All screening labs should be performed within 2 weeks before any study imaging procedures are performed.

Table 1 Adequate Organ Function Laboratory Values

| **System** | **Laboratory Value** |
| --- | --- |
| **Hematological** |  |
| White blood cell count (WBC) | ≥2,000 /mcL |
| Absolute neutrophil count (ANC) | ≥1,500 /mcL |
| Platelets | ≥100,000 / mcL |
| Hemoglobin | ≥9 g/dL or ≥5.6 mmol/L |
| **Renal** |  |
| Serum creatinine **OR**  Measured or calculated creatinine clearance  (GFR can also be used in place of creatinine or CrCl) | ≤1.5 X upper limit of normal (ULN) **OR**  ≥30 mL/min for subject with creatinine levels > 1.5 X institutional ULN |
| **Hepatic** |  |
| Serum total bilirubin | Total Bilirubin ≤ 1.5 x ULN (except subjects with Gilbert Syndrome, who can have total bilirubin < 3.0 mg/dL) |
| AST (SGOT) and ALT (SGPT) | ≤ 3 X ULN |

1. Women of childbearing potential (WOCBP) must use appropriate method(s) of contraception during the study and for 23 weeks after the last dose of nivolumab. Women who are not of childbearing potential (i.e. who are postmenopausal or surgically sterile) as well as azoospermic men do not require contraception ([Appendix 4](#Appendix4))
2. Men who are sexually active with WOCBP must use any contraceptive method with a failure rate of less than 1% per year. Men receiving nivolumab and who are sexually active with WOCBP will be instructed to adhere to contraception during the study and for 31 weeks after the last dose of nivolumab ([Appendix 4](#Appendix4)).

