## Exclusion criteria

A subject who meets any of the following criteria will be excluded from participation in this study:

1. Is currently participating in or has participated in a study of an investigational agent within 4 weeks of the first dose of treatment or has not recovered (i.e., ≤ Grade 1 or at baseline) from adverse events due to agents administered more than 4 weeks earlier.
2. Has a known current additional malignancy that is progressing or requires active treatment. Exceptions include basal cell carcinoma of the skin, squamous cell carcinoma of the skin, or in situ cervical cancer that has undergone potentially curative therapy or synchronous head and neck squamous cell carcinoma.
3. If subject received major surgery for any other reason, they must have recovered adequately from the toxicity and/or complications from the intervention prior to starting therapy.
4. Subjects with a condition requiring systemic treatment with either corticosteroids (> 10 mg daily prednisone equivalent) or other immunosuppressive medications within 14 days of day -5. Inhaled or topical steroids, and adrenal replacement steroid > 10 mg daily prednisone equivalent, are permitted in the absence of active autoimmune disease.
5. Has an active autoimmune disease requiring systemic steroid treatment within the past 3 months or a documented history of clinically severe autoimmune disease, or a syndrome that requires systemic steroids.
6. Has evidence of interstitial lung disease or active, non-infectious pneumonitis.
7. Has an active infection requiring systemic therapy.
8. Has a history or current evidence of any condition, therapy, or laboratory abnormality that might confound the results of the trial, interfere with the subject’s participation for the full duration of the trial, or is not in the best interest of the subject to participate, in the opinion of the treating investigator.
9. Has known psychiatric or substance abuse disorders that would interfere with cooperation with the requirements of the trial.
10. Is pregnant or breastfeeding, or expecting to conceive or father children within the projected duration of the trial, starting with the pre-screening or screening visit through 23 weeks after the last dose of trial treatment.
11. Has received prior therapy with an anti-PD-1, anti-PD-L1, anti-PD-L2, anti-CTLA-4 antibody, or any other antibody or drug specifically targeting T-cell costimulation or immune checkpoint pathways.

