| - Sexual abstinence   *Sexual abstinence is considered a highly effective method only if defined as refraining from heterosexual intercourse during the entire period of risk associated with the study drug. The reliability of sexual abstinence needs to be evaluated in relation to the duration of the study and the preferred and usual lifestyle of the participant.*   - It is not necessary to use any other method of contraception when complete abstinence is elected. - WOCBP participants who choose complete abstinence must continue to have pregnancy tests, as specified in Section 2. - Acceptable alternate methods of highly effective contraception must be discussed in the event that the WOCBP participants chooses to forego complete abstinence |
| NOTES:  a Typical use failure rates may differ from those when used consistently and correctly. Use should be consistent with local regulations regarding the use of contraceptive methods for participants participating in clinical studies.  b Hormonal contraception may be susceptible to interaction with the study drug, which may reduce the efficacy of the contraceptive method. Hormonal contraception is permissible only when there is sufficient evidence that the IMP and other study medications will not alter hormonal exposures such that contraception would be ineffective or result in increased exposures that could be potentially hazardous. In this case, alternative methods of contraception should be utilized.  c Intrauterine devices and intrauterine hormone releasing systems are acceptable methods of contraception in the absence of definitive drug interaction studies when hormone exposures from intrauterine devices do not alter contraception effectiveness |

| **Unacceptable Methods of Contraception*** |
| --- |
| - Male or female condom with or without spermicide. Male and female condoms cannot be used simultaneously - Diaphragm with spermicide - Cervical cap with spermicide - Vaginal Sponge with spermicide - Progestogen-only oral hormonal contraception, where inhibition of ovulation is not the primary mechanism of action - Periodic abstinence (calendar, symptothermal, post-ovulation methods) - Withdrawal (coitus interruptus). - Spermicide only - Lactation amenorrhea method (LAM) |

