*** Local laws and regulations may require use of alternative and/or additional contraception methods.**

CONTRACEPTION GUIDANCE FOR MALE PARTICIPANTS WITH PARTNER(S) OF CHILD BEARING POTENTIAL.

Male participants with female partners of childbearing potential are eligible to participate if they agree to the following during the treatment and until the end of relevant systemic exposure.

- Inform any and all partner(s) of their participation in a clinical drug study and the need to comply with contraception instructions as directed by the investigator.
- Male participants are required to use a condom for study duration and until end of relevant systemic exposure defined as 7 months after the end of study treatment.
- Female partners of males participating in the study to consider use of effective methods of contraception until the end of relevant systemic exposure, defined as 7 months after the end of treatment in the male participant.
- Male participants with a pregnant or breastfeeding partner must agree to remain abstinent from penile vaginal intercourse or use a male condom during each episode of penile penetration during the treatment and until 7 months after the end of study treatment.
- Refrain from donating sperm for the duration of the study treatment and until 7 months after the end of study treatment.

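### The contraception and pregnancy-test rules in 4.1, 4.2 no. 10, 7.11/7.19 and Appendix 4 disagree on men's period, men's method and the testing of abstinent women

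*Protocol*

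**What the plan says.** **Men's period.** The criterion for men in 4.1 has them "adhere to contraception during the study and for 31 weeks after the last dose of nivolumab". Appendix 4, in its guidance for male participants, sets 7 months after the end of study treatment. Exclusion 10 in 4.2 applies to anyone who is pregnant or breastfeeding or who expects to conceive or to father children, and it runs "starting with the pre-screening or screening visit through 23 weeks after the last dose of trial treatment". It gives one end date for both sexes.

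**Men's method.** Section 4.1 states: "Men who are sexually active with WOCBP must use any contraceptive method with a failure rate of less than 1% per year", and the criterion refers to Appendix 4. There the rule is: "Male participants are required to use a condom for study duration and until end of relevant systemic exposure defined as 7 months". The partner's side is softer: "Female partners of males participating in the study to consider use of effective methods of contraception". The table of highly effective methods in the same appendix carries the standard of under 1% per year and does not include condoms. The table of unacceptable methods begins with "Male or female condom with or without spermicide". Both tables stand under the guidance for female participants.

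**Pregnancy tests.** In the entry on sexual abstinence, Appendix 4 says: "WOCBP participants who choose complete abstinence must continue to have pregnancy tests, as specified in Section 2". Section 2 is Objectives and Hypotheses and contains nothing on testing. Section 7.11 provides one additional serum tube for β-HCG at screening for WOCBP. The schedule in 7.19 has one mark for the pregnancy test, in the screening column.

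**The concern.** These are binding eligibility and safety rules. A site has to apply 4.1, 4.2 and Appendix 4 together when it screens and counsels a patient, and 4.1 itself sends the site to Appendix 4. If these places give different end dates, different standards of method and a test reference that leads nowhere, two sites, or two physicians at one site, can treat the same patient differently while each follows the text.

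The subject bears on patient safety. Section 8.1.2 requires pregnancy to be handled as a serious adverse event, and 8.3 extends reporting to pregnancies in partners of male participants. The issue does not touch what the trial measures or how it is analysed.

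**Working it through.** No sample size, power or alpha figure is involved. The check converts the periods to a common unit and sets the rules side by side, taking one month as 365.25 / 12 = 30.44 days.

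**Step 1: periods for men.**
- 4.1: 31 × 7 = 217 days.
- Appendix 4: 7 × 30.44 = about 213 days.
- Exclusion 10: 23 × 7 = 161 days.

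4.1 and Appendix 4 differ by 217 − 213 = about 4 days, which is a difference between weeks and months and no real conflict. Exclusion 10 falls short of 4.1 by 217 − 161 = 56 days (8 weeks; 8/31 = 26% of the 31-week period), and of Appendix 4 by 213 − 161 = about 52 days. The duration conflict therefore lies between exclusion 10 and the other two places.

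**Step 2: where the 23 weeks agrees.** For women, 4.1 also sets 23 weeks (161 days), and Appendix 4 sets 5 months (5 × 30.44 = about 152 days, some 9 days less). Exclusion 10 thus matches the 4.1 period for women exactly and does not match the period for men, although its wording includes men.

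**Step 3: method for men.**

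| Place | Requirement |
|---|---|
| 4.1 | a method with a failure rate under 1% per year; see Appendix 4 |
| Appendix 4, male guidance | a condom; partner to consider an effective method |
| Appendix 4, highly effective methods | condoms not listed |
| Appendix 4, unacceptable methods (female guidance) | condoms listed |

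A man who uses a condom and does nothing more meets the male guidance. Nothing in the protocol shows that he meets 4.1, because the only list tied to the under-1% standard omits his method. A man who uses a condom and also relies on a listed method, for example one used by his partner, can meet both.

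**Step 4: pregnancy tests.**
- Tests required of abstinent WOCBP by Appendix 4: continuing, with times to be found in Section 2.
- Tests specified in Section 2: none.
- Tests in 7.11 and 7.19: one, at screening.
- Scheduled tests after screening: 0.

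The cross-reference is wrong on any reading. Whether tests are also missing from the schedule depends on what continuing to have tests was meant to require, and the text does not settle that.

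**The case against.** The strongest reply is that these are wording faults with little practical effect. Four parts of it deserve an answer.

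- **Method.** Appendix 4 nowhere says that a condom alone suffices, the table of unacceptable methods is addressed to female participants, and no failure rate for condoms is given. All of this is correct. A reader might infer that any man following Appendix 4 fails inclusion, and the documents do not support that. What stands is that the appendix to which 4.1 refers does not repeat the 4.1 standard and requires something that is not on its own list.
- **Period.** A man must meet all inclusion criteria as well as no exclusion, so 4.1 still binds him for the study and for 31 weeks. Follow-up runs to 12 months after surgery. With nominal dosing on day 3 and surgery on day 25, that is 25 + 365 − 3 = 387 days after the dose, beyond both 161 and 217 days for a man who completes it. A reader might infer from the 56-day gap that exposure goes uncovered, and that does not follow. What stands is that exclusion 10, as a screening question, passes a man who already expects to act against the instruction in 4.1.
- **Testing.** The Appendix 4 sentence may mean only that abstinence does not exempt a woman from whatever tests are scheduled. On that reading the fault is the reference alone. The opening of section 7 also allows unscheduled procedures when clinically necessary, so it would be wrong to infer that an abstinent woman is never tested again. The reference to Section 2 still needs correcting, and the intended meaning needs stating.
- **Safety data.** Reporting of pregnancies in participants and in partners is laid down in 8.1.2 and 8.3. No loss of reporting is shown.

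**Conclusion.** The reproductive-risk rules contradict one another as written, in three places: an 8-week difference between exclusion 10 and the rules for men elsewhere; a method standard for men in 4.1 that the requirement in Appendix 4 does not carry over; and a pregnancy-test reference to a section without tests, against a schedule with a single test at screening.

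Confidence is high on the 23 versus 31 weeks and on the wrong cross-reference, since both can be read directly from the text. The point on method rests on taking the appendix's own list as its statement of what meets the under-1% standard. The point on testing, beyond the wrong reference, depends on how the sentence on abstinence is read.

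The rules reach every enrolled man who is sexually active with a WOCBP, and the testing sentence reaches WOCBP who choose abstinence. The protocol does not say how many of the 15 planned evaluable patients these would be. The matter should be corrected because it governs eligibility and safety, but it has no bearing on endpoints, analyses or sample size.

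**What to change.** Reconcile 4.1, 4.2 no. 10 and Appendix 4 so that each sex has one consistent statement of method and one of period, in one unit of time, with the other places referring to it. Say explicitly whether exclusion 10 is meant to have one end date for both sexes. State whether the 4.1 method standard applies to the male guidance in Appendix 4, and make the two texts agree. Replace the reference to Section 2 with one to the place where pregnancy tests are specified, and make that place, 7.11 and 7.19 agree with what Appendix 4 asks of abstinent women. Which method, period and test times apply is for the sponsor to decide.

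The cost is wording in four places of the protocol, matching text in the patient information, and notification of the amendment to the ethics committee under 11.4. No analysis changes.

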## Exclusion criteria

A subject who meets any of the following criteria will be excluded from participation in this study:

1. Is currently participating in or has participated in a study of an investigational agent within 4 weeks of the first dose of treatment or has not recovered (i.e., ≤ Grade 1 or at baseline) from adverse events due to agents administered more than 4 weeks earlier.
2. Has a known current additional malignancy that is progressing or requires active treatment. Exceptions include basal cell carcinoma of the skin, squamous cell carcinoma of the skin, or in situ cervical cancer that has undergone potentially curative therapy or synchronous head and neck squamous cell carcinoma.
3. If subject received major surgery for any other reason, they must have recovered adequately from the toxicity and/or complications from the intervention prior to starting therapy.
4. Subjects with a condition requiring systemic treatment with either corticosteroids (> 10 mg daily prednisone equivalent) or other immunosuppressive medications within 14 days of day -5. Inhaled or topical steroids, and adrenal replacement steroid > 10 mg daily prednisone equivalent, are permitted in the absence of active autoimmune disease.
5. Has an active autoimmune disease requiring systemic steroid treatment within the past 3 months or a documented history of clinically severe autoimmune disease, or a syndrome that requires systemic steroids.
6. Has evidence of interstitial lung disease or active, non-infectious pneumonitis.
7. Has an active infection requiring systemic therapy.
8. Has a history or current evidence of any condition, therapy, or laboratory abnormality that might confound the results of the trial, interfere with the subject’s participation for the full duration of the trial, or is not in the best interest of the subject to participate, in the opinion of the treating investigator.
9. Has known psychiatric or substance abuse disorders that would interfere with cooperation with the requirements of the trial.
10. Is pregnant or breastfeeding, or expecting to conceive or father children within the projected duration of the trial, starting with the pre-screening or screening visit through 23 weeks after the last dose of trial treatment.
11. Has received prior therapy with an anti-PD-1, anti-PD-L1, anti-PD-L2, anti-CTLA-4 antibody, or any other antibody or drug specifically targeting T-cell costimulation or immune checkpoint pathways.
12. Has a known history of Human Immunodeficiency Virus infection with a detectable viral load. Patients with an undetectable load (<50 copies/ml) receiving adequate anti-retroviral therapy, are allowed to participate.
13. Has known active Hepatitis B or C.

## Sample size calculation

Since this is a pilot feasibility study to investigate safety and tolerability, [^18^F]BMS-986192 and [^18^F]-FDG PET imaging before and on treatment with nivolumab, a sample size of 15 evaluable patients has been chosen. The objective of this study is descriptive and hypothesis generating, so no formal statistical justification for the sample size is provided.

# PET IMAGING WITH [18F]BMS-986192 and [18F]-FDG AND NIVOLUMAB TREATMENT

## Radiolabeling of [18F]BMS-986192

[^18^F]BMS-986192 will be radiolabeled according to radiochemical procedures that have been developed at VUmc and BMS. A Good Manufacturing Practice (GMP) compliant method has been set up and [^18^F]BMS-986192 can be produced according to GMP guidelines under the GMP manufacturing license for radiopharmaceuticals of the department of Radiology and Nuclear Medicine. Please refer to the Investigational Medicinal Product Dossier (IMPD) for further details.

## [^18^F]BMS-986192 injection procedure

The injections will take place at the department of Nuclear Medicine & PET research. Before treatment with nivolumab, a tracer dose of 225 MBq ±10% of [^18^F]BMS-986192 will be injected as a bolus of up to 10 ml through an injector (Medrad International, Maastricht, The Netherlands) at 0.8 ml/s, after which the line will be flushed with 10 mL physiologic saline. A second injection of [^18^F]BMS-986192 will be given 21 ±3 days after treatment with nivolumab to the same schedule (see [Schedule of assessments 7.19](#_Schedule_of_Assessments)).

## [^18^F]BMS-986192/[^18^F]-FDG PET procedure

All PET scans will be performed on a Philips Ingenuity TF PET/CT scanner. Each acquisition will start with a 30 mAs low-dose CT scan to correct for attenuation of the subsequent emission scan. A static total body PET scan after injection of 225 MBq ±10% [^18^F]BMS-986192 will be acquired at 60-75 min post injection. Static acquisition consists of 10-12 bed positions, depending on the length of the patient, of 3 minutes each.

[^18^F]-FDG PET will be performed in compliance with European Association of Nuclear Medicine (EANM) 2.0 guidelines [59], before and 21 ±3 days after start of treatment with nivolumab. Briefly, patients will fast 6 hours prior to the radiotracer injection. Patients will be injected with 3 MBq/kg (± 10%) [^18^F]-FDG. After 60 min (± 5 min) a PET scan will be performed from skull base to mid-thigh. The dose of [^18^F]-FDG will be about 185 MBq for PET (adapted by weight). Residual activity in the syringe will be measured and subtracted from the injected dose before calculations are done.

[^18^F]-FDG-PET and [^18^F]BMS-986192 PET will be performed with a minimum interval of 24 h to allow sufficient decay of the remaining tracer.

## Radiation exposure

For the patient the radiation dose of administering 225 ±10% MBq of [^18^F]BMS-986192 or [^18^F]-FDG is expected to be around 4.5 mSv each. Low dose CT scans used for attenuation correction will give an additional dose of 3 mSv per scan. The dose attributed to study procedures is therefore expected to be 22-23 mSv. The total radiation exposure (including standard of care) is expected to be 39-41 mSv. After injection no shielding is required and the patient can go home immediately.

## Analysis of PET data

### [18F]BMS-986192 PET

All PET data will be normalized and corrected for randoms, tissue attenuation, decay, scatter and dead time. PET-CT data will be reconstructed with TF-OSEM, resulting in a transaxial spatial resolution of ~7 mm in the centre of the field of view. Volumes of interest (VOIs) will be defined using the CT images which are co-registered to the PET-CT data and using a threshold technique [59, 65, 66]. The maximum pixel value within the tumor (SUV_max_), the 3D SUV_peak_, a threshold defined volume of interest providing SUV_mean_ and a manually CT defined volume (SUV_CT_) will be derived for any lesion with adequate focal uptake (50-53).

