### Rationale for endpoints

This is a feasibility study of neoadjuvant nivolumab in locally advanced oral cancer combined with [^18^F]BMS-986192 and [^18^F]-FDG PET as well as immuno-monitoring and DNA profiling on tissue and blood in order to identify biomarkers for response and investigate safety.

The primary endpoint of this study is [^18^F]BMS-986192 uptake in tumor lesions and safety and tolerability of neoadjuvant nivolumab. [^18^F]BMS-986192 tumor uptake will be quantified, tumor uptake heterogeneity between patients and within and between tumor lesions of the same patient will be assessed. These results will be correlated with [^18^F]-FDG uptake, as effective treatment with immune therapy may lead to increase in early [^18^F]-FDG uptake, as well as to (pathological) response.

The secondary endpoints include the correlation of the imaging and response data to measured blood and tissue parameters. The immune status will be assessed in the tumor by multiplex immunostaining (see section 3.10.1) and in peripheral blood and TDLN by flowcytometry for the frequency and activation status of immune subsets (see section 3.8). Cytokine profiling may be performed in plasma or from TDLN in ex vivo O/N cultures.

In addition, the presence of neoantigens and the molecular background of the tumor as copy-number-high or copy-number-silent will be determined. Neoantigen analysis will be performed by DNA sequencing using a combined approach of low coverage whole genome sequencing for copy numbers, and exome enrichment sequencing for mutations. Normal DNA from blood will be analyzed in parallel to filter SNPs. In addition RNA sequencing will be performed and the data mined as previously described [53].

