# OBJECTIVES AND HYPOTHESES

## Primary objectives & hypotheses

1. To investigate heterogeneity in tumor uptake of [^18^F]BMS-986192 between patients and within tumor lesions of the same patient (primary tumor and TDLN/lymph node metastases) before treatment, in relation to changes in [^18^F]-FDG uptake before and on treatment

*Hypothesis: interpatient and intrapatient heterogeneity in tumor accumulation of [^18^F]BMS-986192 is expected and can be visualized. [^18^F]-FDG allows identification of viable tumor.*

2. To investigate the feasibility and safety of neoadjuvant nivolumab immunotherapy prior to surgery for locally advanced oral cancer.

*Hypothesis: neoadjuvant immunotherapy with nivolumab is feasible and safe, and will lead to immune activation and clinical response in a subset of patients.*

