# ENDPOINTS

## Main study parameters/endpoints

PET Imaging

[^18^F]BMS-986192 and [^18^F]-FDG SUV_max_, SUV_mean,_ SUV_peak_ will be measured in all tumor lesions and (enlarged) lymph nodes using manually drawn volumes of interest (VOI) before and on treatment. For [^18^F]BMS-986192 manually drawn VOIs will also be calculated for liver, kidneys, lungs, spleen and left ventricle of the heart.

(Serious) adverse events

We will pay special interest to all adverse events during the study, in order to obtain information on safety and tolerability of neoadjuvant nivolumab in patients with locally advanced oral cancer who are planned for treatment with curative intent including surgery.

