## Secondary study parameters/endpoints

#### Heterogeneity analysis

#### Interpatient, intrapatient and intratumor SUV heterogeneity.

Correlation between both PET scans, and between imaging and response

The correlation between SUV for [^18^F]BMS-986192 and [^18^F]-FDG baseline and on treatment and early response evaluation with [^18^F]-FDG.

Correlation between PET data and Blood/Tissue markers

The correlation between continuous values as SUV and the categorical variables tissue PD-1 and PD-L1 IHC will be assessed for each tumor lesion. Correlation with immuno-monitoring analysis in tumor tissue/lymph nodes and blood, plasma vesicle miRNAs from blood, as well as DNA/RNA profiling in tumor tissue at baseline and at surgery will be assessed.

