# STATISTICAL ANALYSIS

## Analysis of PET data

SUV_max_, SUV_mean_ and SUV_peak_ (both tracers) will be measured for all tumor lesions and enlarged lymph nodes. For ^18^F-FDG also MTV and TLG will be determined.

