#### Heterogeneity analysis

### Interpatient heterogeneity

Test-retest variability of PET using modern machines is ~15% (62-64). Therefore, uptake difference between patients (interpatient heterogeneity) is defined as SUV differences of 15% or greater.

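### Section 5.5.1 ties every [18F]BMS-986192 SUV to an undefined uptake condition, while Sections 6.1, 6.2 and 9.1 call for SUVs in all lesions

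*Protocol*

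**What the plan says.** Four places in the protocol bear on which lesions receive a PD-L1 tracer SUV.

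- Section 5.5.1 ([18F]BMS-986192 PET) lists SUVmax, SUVpeak, a threshold-based SUVmean and SUV_CT from a manual CT volume. It says that these "will be derived for any lesion with adequate focal uptake". Adequacy is not defined there or elsewhere.
- Section 6.1 (main endpoints) says that SUVmax, SUVmean and SUVpeak of both tracers "will be measured in all tumor lesions and (enlarged) lymph nodes using manually drawn volumes of interest (VOI) before and on treatment".
- Section 9.1 (statistical analysis) says that the same three measures, again for both tracers, "will be measured for all tumor lesions and enlarged lymph nodes".
- Section 6.2 (secondary endpoints) says that the correlation of SUV with tissue PD-1 and PD-L1 staining "will be assessed for each tumor lesion".

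The first primary objective (Section 2.1) is "To investigate heterogeneity in tumor uptake of [^18^F]BMS-986192 between patients and within tumor lesions of the same patient", before treatment. Section 1.2.7 names as primary endpoint the tracer's "uptake in tumor lesions and safety and tolerability of neoadjuvant nivolumab". For interpatient heterogeneity, the heterogeneity part of Section 9 states that "uptake difference between patients (interpatient heterogeneity) is defined as SUV differences of 15% or greater".

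**The concern.** The condition in Section 5.5.1 selects lesions on the variable under study. A tumor or node with little PD-L1 tracer uptake is a valid observation at the low end of the distribution. Under 5.5.1 as worded it has no SUV.

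Three uses of the data would suffer:

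- **Interpatient spread.** A patient whose lesions all take up little tracer would contribute nothing, and the low end of the comparison would disappear.
- **SUV against staining.** Low-SUV lesions anchor this comparison. Sections 3.4 and 7.16 allow extra biopsies where the two tracers disagree. An FDG-avid lesion with little PD-L1 tracer uptake is such a case, and it could have a staining result with no SUV to pair with it.
- **Change on treatment.** If adequacy is judged separately on each scan, a lesion that loses uptake after nivolumab would lose its second value.

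The condition also covers SUV_CT. A volume drawn on CT needs no tracer uptake, so the one measure that would avoid the selection is restricted without technical need.

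**Working it through.** **Step 1: the rules side by side.**

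| Section | Lesions with an SUV | Uptake condition |
|---|---|---|
| 5.5.1 | those with adequate uptake, undefined | yes, on all four measures including SUV_CT |
| 6.1 | every tumor lesion and enlarged node, both time points | none |
| 6.2 | each tumor lesion, for the staining correlation | none |
| 9.1 | every tumor lesion and enlarged node | none |

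A low-uptake lesion has an SUV under three sections and none under 5.5.1 as worded. No text says which governs. Sections 5.5.1 and 6.1 also differ on how the volume is drawn: CT-based and threshold in the first, manual in the second.

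**Step 2: direction of the effect.** The plan gives no figure to reproduce, so this step is an illustration.

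*Inputs from Section 1.1.4 (earlier lung cancer study, 7 patients):* SUV 3.4 ± 2.9 for lesions below 50% PD-L1 staining, and 7.1 ± 6.0 for lesions at or above 50%.

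*Assumptions not in the protocol:* lognormal SUVs, equal numbers of low and high lesions, one lesion per patient, and a visibility cut-off t between SUV 1 and 3.

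*Formulas:* σ² = ln(1 + (SD/mean)²); μ = ln(mean) − σ²/2; share dropped = Φ((ln t − μ)/σ).

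- Low group: σ² = ln(1 + (2.9/3.4)²) = 0.547, σ = 0.739, μ = 1.224 − 0.273 = 0.950.
- High group: σ² = ln(1 + (6.0/7.1)²) = 0.539, σ = 0.734, μ = 1.960 − 0.269 = 1.691.
- At t = 1.5 (ln t = 0.405): low Φ(−0.74) = 23% dropped; high Φ(−1.75) = 4% dropped.
- At t = 3 (ln t = 1.099): low Φ(0.20) = 58% dropped; high Φ(−0.81) = 21% dropped.

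The last two columns below come from a simulation of 2,000,000 lesions per group.

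| Cut-off (SUV) | Low lesions kept | High lesions kept | CV of SUV, all lesions | Ratio of mean SUV, high to low |
|---|---|---|---|---|
| none | 100% | 100% | 0.96 | 2.09 |
| 1.0 | 90% | 99% | 0.92 | 1.94 |
| 1.5 | 77% | 96% | 0.87 | 1.79 |
| 2.0 | 64% | 91% | 0.82 | 1.66 |
| 3.0 | 42% | 79% | 0.73 | 1.48 |

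The SD of log SUV falls from 0.824 to 0.671 at a cut-off of 1.5, and to 0.535 at 3. The log variance therefore falls by 1 − (0.671/0.824)² = 34% and 1 − (0.535/0.824)² = 58%.

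The shrinkage is in relative spread, the scale on which the 15% interpatient rule is set. The absolute SD (CV × mean) does not fall: it is 0.965 × 5.25 = 5.07 with all lesions and 0.725 × 7.49 = 5.43 at a cut-off of 3. The staining contrast shrinks on both scales: the difference in means goes from 3.71 with all lesions to 8.44 − 5.70 = 2.74 at a cut-off of 3.

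**The case against.** The strongest reply is that 5.5.1 is a paragraph on image processing. It says what is derived where uptake is adequate, and it does not say that other lesions get nothing. A threshold volume does need focal uptake, and Sections 6.1 and 9.1, which define the endpoint and its analysis, prescribe SUVs for all lesions. On that reading no bias arises. This is plausible, and it rules out saying that the protocol measures only visible lesions. It does not remove the point, because the condition also covers the CT-drawn SUV and the document leaves a reader with two rules.

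A reader might infer four stronger things that the documents do not support:

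- **That intrapatient heterogeneity is numerically biased.** Section 9.2.2 assesses it qualitatively. A non-avid node beside an avid primary is itself a visible difference and needs no SUV.
- **That a lesion losing uptake necessarily loses its second value.** Section 5.5.1 does not say that adequacy is judged scan by scan, and 6.1 specifies both time points. Change in PD-L1 tracer uptake is also a secondary objective; the first primary objective concerns that tracer's uptake before treatment.
- **That the percentages above predict the loss.** The cut-offs have no source in the protocol, and the inputs come from 7 patients with another cancer. Section 1.1.4 reports visible uptake in all of them and calls a mean of 3.4 moderate, which fits poorly with a cut-off of 3 that discards 58% of low lesions.
- **That the tabulated summaries are planned analyses.** They are not. Section 9 gives the 15% rule and an ANOVA for staining. With 15 patients, sampling error would exceed shifts of this kind.

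A definition of adequate uptake could sit in an analysis plan that is not shown. The conflict between sections is in the protocol itself.

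**Conclusion.** The contradiction is established from the text: 5.5.1 conditions every PD-L1 tracer SUV on undefined uptake, while 6.1, 6.2 and 9.1 carry no such condition. The bias is conditional on 5.5.1 being the rule followed. Its direction then follows from removing low values: relative interpatient spread is understated and the SUV-staining comparison is weakened. Loss of on-treatment values is possible but is an inference. The size cannot be stated while adequacy is undefined.

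This should be fixed, but it does not undermine the trial. The study is descriptive and hypothesis generating (Section 4.3), which makes an undistorted picture of uptake its main imaging product. The repair is a small wording change.

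**What to change.** Amend Section 5.5.1 to agree with 6.1 and 9.1:

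1. Quantify [18F]BMS-986192 uptake in every tumor lesion and enlarged node identified on CT, MRI or FDG PET, at both time points, from the CT-defined or manually drawn volume, whatever the tracer uptake.
2. Keep the uptake condition for threshold-defined volumes only, where it has a technical purpose, and define it.
3. Record visibility on the PD-L1 tracer scan as a separate yes/no variable for each lesion and scan.
4. In the same edit, align the description of how volumes are drawn in 5.5.1 and 6.1.

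The cost is a short text change and a few more volumes per scan, with no extra scan or patient burden. The drawback is that SUVs of low-uptake lesions are noisier. That is preferable to values missing because they are low, and the visibility variable lets a reader see which values are affected.
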